### Interim analyses {21b}

Not applicable; no interim analysis is planned for this study.

### Methods for additional analyses (e.g. subgroup analyses) {20b}

Not applicable, no additional analysis is planned for this study.

### Methods in analysis to handle protocol non-adherence and any statistical methods to handle missing data {20c}

This is an intention-to-treat study and we will explain the intervention in detail and emphasise matters of cooperation to patients during the pre-anaesthetic assessment and during obtaining informed consent, we suspect that few patients will offer non-compliance with the protocol. In the event of missing data, we will complete the data set by using multiple compensation methods as recommended by the statistical experts Hsu et al. [15] and will assess its effect by sensitivity analysis. We anticipate that few patients will be lost to follow-up due to the nature of clinical practice of the current trial intervention.

### Plans to give access to the full protocol, participant-level data and statistical code {31c}

This is a principal investigator-initiated trial. Access to the full protocol, participant-level data and statistical code for research purposes will be considered upon submission of a reasonable written request and obtaining authorization from the principal investigator.

## Oversight and monitoring

### Composition of the coordinating centre and trial steering committee {5d}

This is a single centre trial and there will be no coordinating centre or trial steering committee. The principal investigator will hold weekly study team meetings to discuss and analyse the progress of the study and to report any serious incidents to the Ethics Committee. There will be no stakeholder or private sector involvement.

### Composition of the data monitoring committee, its role and reporting structure {21a}

We expect to rapidly complete the clinical intervention trial, there is no evidence of significant safety concerns with this study intervention, the participants are not involved in specific disease groups or life-threatening conditions and therefore no specific data monitoring committee will be established. The “data monitoring team” involved in item 19 is responsible for verifying source documents and possible adverse events, and the membership of this team and the process of verification will be independent of the study process.

### Adverse event reporting and harms {22}

Adverse events, adverse drug reactions, unexpected adverse drug reactions, and serious adverse drug reactions will be defined according to the guidelines for good clinical practice of the Quality Management Standards for Drug Clinical Trials in China [16]. We will assess the nature (expected versus unintended), severity (serious versus non-serious) and relevance to the intervention (relevant versus irrelevant) of each adverse event. Serious, unintended and intervention-related adverse events will be reported to the Ethics Committee. The principal investigator will conduct regular reviews of all adverse events and convene adverse event assessment discussion meetings as necessary. Any adverse events that occur in this trial will be recorded on the CRF and reported to the principal investigator. In the meantime, subjects will be followed until they are deemed to have fully recovered or overcome the adverse event.

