**Discussion:**

Analgesia after MRM surgery is important and chronic pain can develop when acute pain is prolonged, but the analgesic effect of a nerve block with a single injection of LA is limited by the duration of drug action. The aim of this trial is to investigate whether continuous ESPB can reduce acute pain after MRM surgery and reduce the incidence of chronic pain (PMPS), with fewer postoperative analgesic drug-related complications and less inflammatory response. Continuous ESPB and up to 12 months of follow-up are two innovations of this trial.

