## Objectives {7}

We hypothesised that ultrasound-guided continuous ESPB would reduce the amount of analgesic medication used during and after surgery and reduce the level of pain during catheter retention, thereby reducing the short-term side effects associated with anaesthesia and decreasing the incidence of post-surgical inflammatory reactions and chronic pain. To test this hypothesis, two groups of patients undergoing MRM surgery will be compared: group E received a continuous ESPB and group C received a sham puncture. The main aim of this study is to test the hypothesis that continuous nerve block overcomes the temporal limitations of a single injection of drug and provides longer analgesia, thereby reducing analgesic drug consumption, inflammatory response and the incidence of PMPS.

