#### Secondary outcomes

The static and dynamic pain scores at 2, 6, 12, 24 and 48 h postoperatively. Pain is scored using a visual analogue scale (VAS), with a score of 0–10 representing pain levels ranging from no pain at all to intolerably severe pain. Dynamic pain is the pain felt when the arm is externally rotated 45° on the side of the operation.The occurrence of PMPS. Defined as chronic pain not related to incision healing, which may be burning pain, pins and needles, tenderness-induced pain, or deep dull pain at the surgical or surgery-related site, and which occurs for at least 4 days in a week after surgery [10, 11].The levels of inflammation-related cytokines. Concentrations of CRP, IL-6, IL-10 and TNF-α in venous blood 1 day before, 2, 6, 12, 24 and 48 h after surgery.Concentration of ropivacaine in venous blood 1, 2 and 3 days after surgery.Total consumption of additional analgesics. Remedial analgesia using parecoxib sodium dosage and the use of additional analgesics during the entire 12-month follow-up period.Post-operative adverse reactions. Including but not limited to PONV, drowsiness, itching, respiratory depression and urinary retention.Post-puncture adverse reactions. Including but not limited to haematoma, infection, nerve damage and abnormal sensation in the blocked area.Postoperative recovery, including the length of stay in PACU, time of first ambulation, intake of food, voiding, gastrointestinal function, length of stay in hospital and the quality of Recovery-15 (QoR-15) questionnaire at 24 h and 48 h after surgery and on the day of discharge [9]. Discharge criteria: vital signs are normal; wound healing is good, with no obvious postoperative complications, such as wound infection, flap necrosis, or fluid accumulation due to poor drainage; pain is mild and does not require medication or oral analgesic medication to achieve satisfactory analgesia; gastrointestinal function is normal; able to get out of bed and move around freely; intravenous fluids are not required; and the patient is willing and wants to be discharged from the hospital.

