## Statistical methods

### Statistical methods for primary and secondary outcomes {20a}

Statistical analysis will be performed using SPSS statistical software version 27.0 (IBM). All statistical tests will be two-tailed and the significance level will be set at 0.05. Primary and secondary outcomes will be analysed using the following statistical method: the Kolmogorov–Smirnov test will be used to determine whether continuous data follow a normal distribution, and the Levene’s test was used to assess the homogeneity of variance. Normally distributed continuous data are expressed as mean ± standard deviation and compared using the independent samples* t*-test. Non-normally distributed continuous data will be expressed as median and interquartile range and compared by the Mann–Whitney *U* test. Count data is expressed as the number of cases (rate) by the chi-square test or Fisher’s exact test.

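### The protocol's severity rule for adverse events records seriousness, a reporting category, so mild and severe non-serious events are not told apart; incidence can still be compared

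*Protocol article*

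**What the plan says.** Adverse event reporting and harms {22} sets three assessments for every adverse event: whether it was expected, its severity, and its relation to the intervention. The second is given as "severity (serious versus non-serious"). The section then states what leaves the site: "Serious, unintended and intervention-related adverse events will be reported to the Ethics Committee". For the definitions of the event classes it points to an outside standard; these "will be defined according to the guidelines for good clinical practice" in force in China. The classes named there are adverse events and adverse drug reactions, including unexpected and serious ones. No intensity scale is mentioned.

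Two of the secondary outcome items under Outcomes {12} are adverse reactions. The post-operative item reads "Including but not limited to PONV, drowsiness, itching, respiratory depression and urinary retention"; the post-puncture item reads "Including but not limited to haematoma, infection, nerve damage and abnormal sensation in the blocked area". Neither carries a grade. For the analysis, Statistical methods {20a} provides: "Count data is expressed as the number of cases (rate) by the chi-square test or Fisher’s exact test".

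The expected benefit is worded in two ways. Objectives {7} has the block "thereby reducing the short-term side effects associated with anaesthesia", which could mean fewer events or milder ones. The Discussion paragraph of the Abstract says "with fewer postoperative analgesic drug-related complications and less inflammatory response", which is a count.

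**The concern.** Seriousness and severity are different attributes. Seriousness classifies an event for reporting, and this protocol uses it to decide what goes to the Ethics Committee. Severity is how intense the event was. An event can be severe without being serious, as prolonged vomiting after surgery often is. The protocol puts the first attribute under the name of the second, so one two-level item fills both roles and intensity has no item of its own.

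Two things are at stake. First, the description of harms: severe but non-serious reactions would be pooled with trivial ones. That matters somewhat more here because no data monitoring committee is planned, and the regular review of adverse events rests with the principal investigator. Second, the comparison of side effects: if the block makes reactions milder without changing how many patients have one, data recorded under the stated rule would not show it.

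**Working it through.** **Step 1. Is intensity graded anywhere else?** The relevant places in the protocol article, side by side:

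| Section | Content | Intensity of an event graded? |
|---|---|---|
| Adverse event reporting and harms {22} | serious / non-serious, under the name severity | No |
| Secondary outcomes under {12} | lists of reactions | No |
| Intervention description {11a}, Preparing | low / medium / high PONV risk before surgery | No; a patient's prior risk, not an event |
| Plans for assessment and collection {18a} | adverse effects are recorded after surgery | No |
| Statistical methods {20a} | counts and rates, chi-square or Fisher | No |

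**Step 2. Which listed reactions would share one category?** PONV, drowsiness, itching, urinary retention and abnormal sensation would ordinarily be non-serious. Respiratory depression, infection or nerve damage could be serious. This is a judgement, because the protocol gives no rates.

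**Step 3. What is lost and what is kept.** The any-event comparison needs only presence or absence, so it is kept. A comparison restricted to moderate-or-severe events needs a grade, so it is lost.

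**Step 4. Illustration of size.** The protocol has no figure on this point to reproduce. Only the number per arm (71, before the dropout allowance, from Sample size {14}), the two-sided test and the 0.05 level are taken from it. That 71 is reproducible from the stated pain scores: the unequal-variance t-test has power 0.799 at 70 per arm and 0.805 at 71. All event rates below are assumptions.

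Power for two proportions with n per arm, where d = p1 − p2 and p̄ = (p1 + p2)/2:

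- SE0 = √[2 p̄(1 − p̄)/n]
- SE1 = √[(p1(1 − p1) + p2(1 − p2))/n]
- power = Φ[(d − 1.96 SE0)/SE1]

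In each scenario the incidence is the same in both arms, so the any-event comparison has no true difference to detect and rejects only at the error rate of 5%.

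*A. Incidence 30%; moderate-or-severe share of events 70% in control, 20% in the block group.* p1 = 0.30 × 0.70 = 0.21; p2 = 0.30 × 0.20 = 0.06. SE0 = √(2 × 0.135 × 0.865/71) = 0.0574; SE1 = √((0.1659 + 0.0564)/71) = 0.0560. Power = Φ[(0.15 − 0.1124)/0.0560] = Φ(0.67) ≈ 75%.

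*B. Incidence 50%, same shares.* p1 = 0.35; p2 = 0.10. SE0 = 0.0701; SE1 = 0.0669. Power = Φ[(0.25 − 0.1374)/0.0669] = Φ(1.68) ≈ 95%.

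*C. Incidence 30%; none/mild/moderate/severe 70/10/10/10% in control and 70/22.5/5/2.5% in the block group.* p1 = 0.20; p2 = 0.075. SE0 = 0.0578; SE1 = 0.0568. Power = Φ[(0.125 − 0.1133)/0.0568] = Φ(0.21) ≈ 58%.

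**Step 5. Would a rank test on the four grades be needed?** Simulated power, 6,000 trials per row, 71 per arm:

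| Assumed pattern (control → block group, none/mild/moderate/severe %) | Any event, chi-square | Rank test on grades |
|---|---|---|
| 40/20/20/20 → 50/35/10/5 (fewer and milder) | about 25% | 69% |
| 40/20/20/20 → 40/45/10/5 (milder only) | 5% | about 41% |
| Same control, uniform odds ratio 0.5 | 55% | 60% |
| 70/10/10/10 → 70/22.5/5/2.5 (milder only, scenario C) | 5% | 8% |

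In scenario C the rank test recovers almost nothing (8%), while the moderate-or-severe proportion has about 58% power with a test that the protocol already plans.

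**The case against.** The strongest reply is that the section on harms is a reporting rule. Expectedness, seriousness and relatedness are the three attributes that trigger a report to the Ethics Committee, and as a trigger they work; only the label is wrong. Serious events are still identified, reported and followed. The lists of reactions, the analysis of counts and the stated aim of fewer complications agree with one another, and all concern incidence. The CRF is not shown and may hold grading fields. Control-arm rates as high as those in some scenarios may also be too pessimistic, since all patients receive antiemetic prophylaxis and the PCIA contains an antiemetic.

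Much of this stands. A reader might infer that the trial cannot show any reduction in side effects. The documents do not support that, because incidence remains testable and is what the Abstract's aim names. A reader might infer that the CRF certainly records nothing about intensity. That cannot be known from the article. A reader might also infer that an ordinal analysis is required. It is not: the aim does not call for one, and its gain depends on the assumed pattern.

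What does not stand is that this is merely detail left to another document. The article states a severity rule for every adverse event and states it wrongly. If the CRF follows that rule, no later analysis plan can restore a grade that was not collected.

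**Conclusion.** The point holds in a limited form. The protocol defines severity by a reporting category, and no section of the article grades the intensity of an adverse event. Under the stated rule, mild and severe non-serious reactions receive the same entry. That most of the listed reactions fall in this group is a reasonable judgement, not a figure in the protocol.

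The consequence is confined to the intensity of secondary safety outcomes. The primary outcome, the sample size and the comparison of how many patients have each reaction are untouched. Under assumed rates with equal incidence in both arms, grading would give roughly 58% to 95% power to detect the chosen shifts in moderate-or-severe events, which an any-event comparison could not detect. Those figures rest wholly on the assumed rates and shifts and should be read as illustration. The firmer reason to act is a better description of harms at very low cost.

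**What to change.** In Adverse event reporting and harms {22}, rename the serious/non-serious item as seriousness and keep it for Ethics Committee reporting. Add a separate intensity grade of mild, moderate or severe for each adverse event, recorded on the CRF, with the meaning of each grade stated in advance. Report by arm the incidence of any event and of moderate-or-severe events, either descriptively or with the chi-square or Fisher test already planned. No rank or proportional-odds analysis is needed.

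The cost is one CRF field, completed at contacts already planned, and a short amendment through the Ethics Committee. Recruitment is under way, so patients already enrolled may lack the grade unless source notes supply it. The report should state how many patients have no grade in each arm.

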## Frequency and plans for auditing trial conduct {23}

A nurse who is not involved in this trial will act as an independent reviewer for the duration of the trial. Independent review will be conducted every 2 weeks or after every 10 newly recruited participants have completed a 48-h post-operative follow-up. All errors will be recorded and reported to the principal investigator. The audit will include a review of CRF content, missing data, duplicate data, incorrect data and informed consent documentation.

### Plans for communicating important protocol amendments to relevant parties (e.g. trial participants, ethical committees) {25}

The Ethics Committee has reviewed the protocol of this study and has given its consent for the study protocol to be carried out. No amendments can be made to the study protocol unless permission is obtained from the Ethics Committee. If a protocol amendment is indeed necessary, it should be reviewed by the principal investigator and a written request for the amendment should be made, and the written request for the amendment will be submitted to the Ethics Committee for further review and approval.

## Dissemination plans {31a}

In accordance with standard protocol guidelines, the authors state that unblinding data from the trial will not be available until the primary outcomes are published. Deblinding will take place at the end of the study. A clinical article will be written on the primary and secondary outcomes of the study and every effort will be made to publish the results in peer-reviewed journals related to clinical anaesthesia and breast surgery, and the results will be disseminated regardless of the size or direction of impact.

## Discussion

Post-operative pain is the most common and urgent acute pain in clinical practice, including incisional pain and inflammatory pain due to surgical trauma, but the control of acute post-operative pain is still unsatisfactory [17]. If acute postoperative pain is not adequately controlled in its initial state, it may develop into chronic postoperative pain and subsequently lead to an inflammatory response, seriously affecting the patient’s postoperative quality of life and increasing the risk of postoperative complications, which in turn affects the patient’s rapid postoperative recovery. Perfect perioperative analgesia is therefore essential.

Regional nerve block techniques, an important component of multimodal analgesia, were used in various types of post-surgical analgesia with definite results. Regional nerve block techniques commonly used in clinical practice for breast surgery include epidural anaesthesia and thoracic paravertebral nerve block, but epidural anaesthesia carries the risk of spinal cord injury and epidural haematoma and is contraindicated in patients with coagulation abnormalities or on anticoagulant medication, and thoracic paravertebral block carries the risk of pneumothorax [18]. Both of these analgesic modalities are difficult to perform and have a high failure rate, making them difficult for beginners to master. Therefore, the search for an effective, simple and safe regional nerve block technique for post-breast surgery analgesia becomes vital. The most significant advantage of the ESPB is that it is simple and safe to perform, and the puncture route is free of vital vessels and organs. The images of the T5 transverse process and the muscle gap are easily identified during the ultrasound-guided procedure [19, 20]. Thus, the ESPB is more feasible than the above two blocking techniques.

Although ESPB was used with definite effectiveness for post-surgical analgesia, most clinical applications were currently for a single injection of LA [7–9]. Theoretically, the maximum duration of a single dose of LA is 12 h [21]. In contrast, continuous administration of the LA after placement of the catheter can provide a longer duration of analgesia. A multicentre, high-quality RCT showed that nerve block with a single injection of LA improved acute pain after breast cancer surgery but did not reduce the incidence of chronic pain [22]. There are still few studies on the use of continuous ESPB in analgesia for MRM surgery, and our research on this occasion is much needed.

Poorly controlled acute pain after surgery is an important contributor to chronic pain and stress and inflammatory responses [23]. We believe that improving acute pain within 48 h of surgery is even more important and therefore used it as the primary outcome for this study. We also evaluated the postoperative recovery in a multidimensional manner by comparing the incidence of PMPS, the QoR-15 score, the concentration of perioperative inflammatory cytokines, total consumption of analgesic agents and post-surgical adverse effects.

In summary, our single-centre, prospective, double-blind RCT will reveal the effect of continuous ESPB on postoperative pain and inflammatory response in patients undergoing MRM surgery and is expected to provide a strong scientific basis for its use in the management of MRM surgery postoperatively. Continuous ESPB and up to 12 months of follow-up are two innovations of this trial. In addition, our results may be extrapolated to other chest procedures and comparisons with the application of different concentrations of local anaesthetics.

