**Methods:**

In this prospective, randomised, controlled trial, we will recruit 160 patients, aged 18–80 years, scheduled for elective MRM surgery under general anaesthesia. They will be randomly assigned to two groups: a continuous ESPB group (group E) and a sham block group (group C). Both groups of patients will have a nerve block (group C pretended to puncture) and an indwelling catheter fixed prior to surgery. Electronic pumps containing LA are shielded. The primary outcome is the total consumption of analgesic agents. The secondary outcomes include the levels of inflammation-related cytokines; the occurrence of chronic pain (post-mastectomy pain syndrome, PMPS); static and dynamic pain scores at 2, 6, 12, 24 and 48 h postoperatively; and post-operative and post-puncture adverse reactions.

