### Outcomes {12}

#### Primary outcome

The primary outcome is the cumulative PCA consumption, including the sum of background dose and self-control dose.

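### Abstract, Outcomes and Discussion name three different primary outcomes, and the sample size rests on a variable listed as secondary

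*Protocol article*

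**What the plan says.** Three sections of the protocol article state the primary outcome.

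- Abstract, Methods: "The primary outcome is the total consumption of analgesic agents".
- Outcomes {12}, Primary outcome: "The primary outcome is the cumulative PCA consumption, including the sum of background dose and self-control dose".
- Discussion: lessening acute pain in the first 48 h "is even more important and therefore used it as the primary outcome for this study".

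Two sections then rank these candidates against one another. The secondary outcomes in Outcomes {12} open with "The static and dynamic pain scores at 2, 6, 12, 24 and 48 h postoperatively", and they include a separate item for parecoxib rescue and other additional analgesics. The Discussion, having called acute pain primary, lists "total consumption of analgesic agents and post-surgical adverse effects" among the things also evaluated.

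Sample size {14} is built on a pain score, dynamic VAS at 48 h, and opens by describing postoperative pain as the trial's focus. Statistical methods {20a} sets a two-tailed 0.05 level for all tests and applies one common set of tests to primary and secondary outcomes alike.

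**The concern.** A confirmatory trial controls its 5% error rate by committing to one test in advance. Here a reader who follows the Abstract, the Outcomes section or the Discussion arrives at a different test each time. The statistical section does not settle the matter, because it ties no single outcome to the confirmatory claim.

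The three variables need not agree. Parecoxib counts towards total analgesic consumption but not towards PCA consumption. A pain score is not a consumption measure at all. A patient whose pain is met by rescue medication can show it in VAS or in parecoxib use while PCA consumption changes little. The trial's headline result could therefore depend on which section is followed.

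The sample size adds to the problem. If PCA consumption is primary, the stated 80% power belongs to a secondary outcome, and the article states no power for the primary one.

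**Working it through.** **1. The candidates side by side**

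| Variable | Abstract | Outcomes {12} | Discussion | Sample size {14} |
|---|---|---|---|---|
| Total analgesic consumption | Primary | Not listed as such; non-PCA part is secondary | Further evaluation | Not used |
| Cumulative PCA consumption | Not named separately | Primary | Not named separately | Not used |
| Acute pain to 48 h | Secondary (pain scores) | Secondary (pain scores) | Primary | Basis (dynamic VAS at 48 h) |

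Loose wording might explain the gap between total and PCA consumption if the article treated the two as the same. It does not, because Outcomes {12} lists the non-PCA analgesics as a separate secondary outcome. Nor can loose wording explain the Discussion, which sets pain and total consumption apart and calls only pain primary. The Discussion also does not say which pain measure is meant (static or dynamic, and at which of five times).

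**2. What the sample size supports**

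Inputs from Sample size {14}: control 4.2 (SD 1.4), ESPB 3.6 (SD 1.1), α 0.05, power 80% (printed as β), 11% dropout. Statistical methods {20a} gives two-sided testing and Sequence generation {16a} gives 1:1 allocation.

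- Difference: 4.2 − 3.6 = 0.6.
- Common SD: √[(1.4² + 1.1²)/2] = √1.585 = 1.259.
- Normal approximation: n = 2 × (1.960 + 0.842)² × 1.585 / 0.6² = 69.1, so 70 per group.
- Exact t-test: power is 0.799 at 70 and 0.805 at 71, so 71 per group, as stated.
- Dropout: 71 / (1 − 0.11) = 79.8, so 80 per group and 160 in total, as stated.

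The arithmetic is correct, but it is the arithmetic for dynamic VAS at 48 h. The article gives no expected mean, difference or SD for PCA or total consumption, so no corresponding figure can be computed for either.

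**3. What free choice among three tests would cost**

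If the confirmatory result could be taken from any of three two-sided 0.05 tests and there were no true effect:

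- Independent tests: 1 − 0.95³ = 0.143.
- Correlated tests (simulated z-tests, equal pairwise correlation, 2 million draws):

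| Assumed correlation | Chance of at least one false positive |
|---|---|
| 0 | 14.3% |
| 0.3 | 13.6% |
| 0.5 | 12.5% |
| 0.7 | 10.9% |
| 0.9 | 8.4% |

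With one fixed primary outcome the figure is 5%. The correlations are assumptions, since the article gives none.

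**The case against.** The strongest reply is that Outcomes {12} is the formal place for the definition. It names exactly one primary outcome and lists pain scores and additional analgesics as secondary. On that view the Abstract is shorthand and the Discussion is loose prose. A statistical analysis plan or registry entry, not available here, may also fix the choice. This stands in part. A reader might infer that the trial has no primary outcome, or that the sponsor means to choose one once the data are in. The document supports neither. It shows contradictory statements and an open risk, and says nothing about intent. The reply does not remove the contradiction, because it is in the current text and the sample size sides with the Discussion.

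A reader might also say that the primary outcome has no time window. The sentence in Outcomes {12} gives none, but Intervention description {11a} runs PCIA until 48 h after surgery and the data collection section {18a} records analgesic consumption over the same 48 h. The window can be inferred and only needs stating.

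The 14.3% figure needs independent tests. That is implausible here, because PCA use is part of total use and all the candidates respond to the same pain. This is why a range is given. A much larger figure is tempting: ten pain readings, each tested at 0.05, would give 1 − 0.95¹⁰ = 40%. It should not be used. It treats repeated readings on the same patients as independent, and no section says that any single reading may be claimed as the primary result.

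Finally, Objectives {7} mentions analgesics used during surgery, and a reader might want intraoperative doses as a named outcome. That is a separate preference with no bearing on how the primary outcome is stated.

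**Conclusion.** The contradiction is real and should be corrected before unblinding. Three sections name three different primary outcomes, and the sample size is attached to a variable that the formal definition makes secondary. The formal definition favours PCA consumption, but the article as a whole leaves open which 0.05 test is confirmatory.

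The possible inflation is from 5% to about 8% to 14%. This is conditional on free choice among three tests and on assumed equal correlations between 0.9 and 0. It measures the risk that the text leaves open and is not an estimate of what will happen. The stated 71 and 80 per group are correct for dynamic VAS at 48 h, but they establish no power for either consumption outcome.

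**What to change.** Before unblinding, and by a dated amendment:

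1. State one primary outcome, with its time window, in the same words in the Abstract, Outcomes {12} and the Discussion. Under the formal definition this is cumulative PCA consumption (background plus self-controlled dose) over the 48 h after surgery, with pain scores and total or additional analgesics secondary.
2. Make Sample size {14} match. Either justify 80 per group for PCA consumption, giving the assumed difference and SD and their source, or say plainly that the 80% power applies to the secondary outcome dynamic VAS at 48 h and that no power is stated for the primary outcome.
3. If the sponsor in fact intends pain as primary, name dynamic VAS at 48 h as the single primary outcome in all these sections. The existing sample size then stands, and PCA consumption becomes secondary.

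The cost is wording in four sections and one submission to the Ethics Committee, plus a source for the consumption assumptions if 80 per group is to be justified for PCA consumption. No new data are needed and no treatment changes. The article says that recruitment is still under way and that unblinding comes at the end of the study, so the change can still be made blind.
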